### Ethical approval

This study was reviewed and approved by Sheffield Research Ethics Committee.

### Statistical methods

The primary analysis will be of accelerometry data at three months post-randomisation. Analysis will be by intention-to-treat. A sensitivity analysis will be undertaken to impute missing accelerometry data using baseline and follow-up data from the group of participants with valid accelerometry data at three months post-randomisation. As this is an ITT analysis, withdrawals and protocol violations will be analysed in their groups as randomised.

All statistical exploratory tests will be two-tailed with alpha = 0.05. Baseline demographic variables (age, gender), physical measurements (e.g. weight, height, BMI), and health-related quality of life data (SF-36) will be summarised with appropriate summary statistics, tabulated and assessed for comparability between the treatment groups. For example, categorical variables, e.g. gender, the number and percentage of each category (e.g. male and female) will be reported. For continuous variables, e.g. age, reporting will depend on the distribution of the data, if it is symmetric, the data will be summarised with a mean and standard deviation; if it has a non-symmetric distribution it will be summarised with a median and inter-quartile range.

The primary aim is to compare the intervention ("full" or "mini" booster) versus control treatment (No booster), with a secondary aim of comparing the two interventions ("full" versus "mini" booster). The primary comparison will be between the mean physical activity levels from the accelerometer (counts per week) in the two "booster" arms combined compared with the mean physical activity levels in the control arm at 6 months follow-up (3 months post-randomisation). This difference in means, between the intervention and control groups, will be compared using a two independent samples t-test and a 95% confidence interval for estimated mean difference between the groups will also be calculated. In the event of differences between the booster and control groups with respect to baseline demographic, physical, and health-related quality of life measurements, multiple regression will be used to adjust the treatment effect for these variables. The ordinary least squares adjusted regression coefficient estimate for the treatment group parameter along with its 95% confidence interval (CI) will then be reported.

The research hypothesis is that the booster intervention groups will have greater levels of physical activity than the control group. The statistical and null hypothesis is that there are no differences between the intervention and control groups at follow up. The alternative hypothesis is that there is a difference in physical activity levels between the intervention and control groups at follow up.

Secondary aims are to compare the effect of the two interventions ("full" versus "mini" booster). This will be done using the same methods as for the primary endpoint as described above. Interim analyses will not be required. An exploratory sub-group analysis using multiple linear regression with the primary outcome, the mean physical activity levels from the accelerometer (counts per week) at 6 months follow-up, will look for an interaction between treatment group (booster or control) and sub-groups defined by gender, ethnicity and access to community facilities (self reported use versus no use of community facilities).

Analyses of secondary outcomes will identify any significant different between groups for each outcome measure, at three months and nine months from randomisation:

1. Physiological measures of fitness (12 minute walk test) and types of physical activity (self report) and change in self-reported physical activity levels

2. Change in health-related quality of life measured by changes in SF-12v2 plus 4 (converted to SF-6D)

3. Health and social care contacts

4. Changes in psychological measures of motivation, intention and stages of change, and self-efficacy

Secondary categorical outcomes such as the proportions maintaining (or increasing) their weekly duration of physical activity in the two "booster" arms combined compared with the proportion in the control arm at 6 months follow-up (3 months post-randomisation), will be compared between the intervention and control groups, using a continuity corrected chi squared test and a 95% confidence interval for estimated differences in proportions will also be calculated. In the event of differences between the groups with respect to baseline demographic, physical, and health-related quality of life measurements, multiple logistic regression will be used to adjust the treatment effect for these variables. The maximum likelihood estimated regression coefficient for the treatment group parameter (odds ratio) along with its 95% confidence interval (CI) will then be reported.

Secondary outcomes such as HRQoL (SF-12v2 plus 4 dimension scores) and distance walked on 12 minute walk test, at three months post-randomisation, will be assumed to be continuous outcomes. A two independent samples t-test will be used to compare mean outcomes between the booster and control groups in this parameter. A 95% confidence interval (CI) for the mean difference in this parameter between the groups will also be calculated. In the event of differences between the booster and control groups with respect to baseline demographic, physical, and health-related quality of life measurements, multiple regression or analysis of covariance (ANCOVA) will be used to adjust the treatment effect for these variables. The ordinary least squares adjusted regression coefficient estimate for the treatment group parameter along with its 95% confidence interval (CI) will then be reported. Outcomes assessed at nine months post-randomisation will be analysed in a similar way. We shall also compare the effect of the two interventions ("full" versus "mini" booster) on these secondary outcomes at three and nine months post-randomisation, using the same methods as described above.

The health economic component of the study will estimate the incremental cost effectiveness of the "mini" booster and full booster interventions compared to no booster. It will include an estimation of the cost effectiveness of the intervention from a NHS perspective in terms of their incremental cost per quality adjusted life year (QALY) and a broader societal assessment of efficiency that includes costs for other Government agencies and productivity (inside and outside the home). It uses similar methods to those used in the successfully completed evaluation of a community exercise programme [22].

There will be two components to the costing. The interventions will be costed, as well as the consequences for the use of health and social services in general. The costs of the booster consultations will be assessed in a micro costing study. The costs will include enrolment of participants, training and time of facilitators, travel and telephone calls. Actual cost data will be collected for consumables and facilitator time will be costed using national grades. Despite being a highly pragmatic trial, there are some features of the programme which are specific to the research study and it will be necessary to adjust for these in order to make the results generalisable. Care will also be taken to compare costs assuming a routine level of throughput, rather than that achieved in the trial. Any research related costs will be excluded.

The consequences for use of health and social services will use resource data collected from participants. Use of primary, secondary, community and social services will be obtained using a self-completed resource questionnaire administered to participants at each assessment at baseline, three months and nine months. Resources will be costed using the best available national estimates. Where appropriate, national unit costs will be used [23].

SF-12v2 plus 4 data will be converted into health state utility values using the SF-6D preference-based algorithm [24]. The area under the curve between assessments will be used to provide an overall estimate of the QALY difference between the intervention arms and the control arm after adjusting for significant baseline variables [25]. Given cost and benefit data will only be collected for nine months, the on-going costs and health benefits will not be discounted, though start-up costs, including training costs, will be annuitised over a five year period. The sensitivity of the results to possible uncertainties in key parameters will be explored by a full sensitivity analysis, including a probabilistic sensitivity analysis.

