### Outcomes

The timing of all outcomes relative to the point of randomisation is shown in Table 1. The primary outcome is seven-day accelerometry, using Actiheart (CamNtech, Cambridge, UK), measured at three months and nine months post-randomisation (see Discussion). Secondary outcomes are:

**Table 1 T1:** Timing of procedures and assessments

	Minus 3 months	Minus 2 months	Minus 1 month	~Minus 1 week	Randomisation	1 month	2 months	3 months	9 months
Brief Intervention Screening Checklist	✔								
SPAQ	✔			✔				✔	✔
DVD (if eligible)	✔								
DVD usage assessment		✔	✔						
Booster Trial Screening Checklist				✔					
Participant Information Sheet				✔	✔				
Participant Consent Form					✔				
BREQ-2					✔			✔	✔
EXERT					✔			✔	✔
Questionnaire 1					✔				
Questionnaire 2					✔			✔	✔
Questionnaire 3 (SF-12v2+4)					✔			✔	✔
Height & weight					✔			✔	✔
Randomisation					✔				
Booster intervention (Rx only)						✔	✔		
12 minute walk test								✔	✔
7 day accelerometery								✔	✔

1. Self-reported moderate or vigorous physical activity using the Scottish Physical Activity Questionnaire (SPAQ) which records type and duration of activities in the previous week;

2. Behavioural Regulation in Exercise Questionnaire (BREQ-2) [18];

3. Exercise Evaluation Randomised Trial (EXERT) questionnaire [19];

4. Health-related quality of life using the Sheffield Version of the 16-item Short Form health survey instrument (SF-12v2 plus 4);

5. Self-reported use of community facilities for physical activity;

6. Self-reported health and social care contacts;

7. Body mass index; and,

8. The 12 minute walk test (physiological measures of fitness) [20].

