### Sample size

For the purposes of sample size estimation the primary outcome is an objective measure of physical activity and will be the mean physical activity levels from the 7-day accelerometric assessment (recoded as counts per week) at 3 months post-randomisation (6 months after initial contact). Kirk and colleagues suggest a standard deviation of approximately 1.2 million counts per week from a 7-day accelerometer assessment of 70 patients with type II diabetes [21]. We assume a mean difference of 400,000 counts per week between the intervention and control groups is the smallest difference of clinical and practical importance that is worth detecting. With 450 subjects (300 intervention: 150 control), the trial will have 90% power to detect this mean difference or greater between the "booster" arm and control arm (assuming a standard deviation of 1.2 million counts/week) as statistically significant at the 5% (two-sided) level using a two independent samples t-test.

With 300 subjects in the booster intervention (150 "mini": 150 "full" booster) the trial will have also have approximately 80% power to detect a similar mean difference of 400,000 counts per week between the two booster arms as statistically significant at the 5% (two-sided) level using a two independent samples t-test. Assuming an approximate 25-30% loss to follow-up by six-months, we proposed to recruit and randomise 200 subjects per group (600 in total). We will invite at least 30,000 40-64 year olds from the 20 most deprived neighbourhoods; we expect at least 1500 will receive the brief intervention of which we anticipate at least 40% will increase their physical activity and be eligible for randomisation. N = 600 divided equally between the three trial arms (200 per arm).

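### Covariate adjustment of the primary comparison depends on observed baseline imbalance, no single primary estimate is named, and baseline SPAQ is not among the listed variables

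*Protocol article*

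**What the plan says.** The Statistical methods section sets the primary comparison as mean accelerometer counts per week at 3 months after randomisation, the two booster arms pooled against control. The means "will be compared using a two independent samples t-test and a 95% confidence interval". This step is unconditional.

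A conditional step follows: "In the event of differences between the booster and control groups with respect to baseline demographic, physical, and health-related quality of life measurements", multiple regression adjusts for those variables and the adjusted coefficient with its 95% interval is reported. No test or threshold defines a difference, no covariate set is fixed in advance, and neither result is named as primary when both exist. The same condition recurs later in the section for the categorical secondary outcomes (logistic regression) and the continuous ones (regression or ANCOVA). It also carries over to full versus mini booster, which uses the same methods.

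The section illustrates its baseline variables with age and gender, with weight, height and BMI as the physical measurements, and with SF-36 for quality of life. Physical activity is not named. Yet Table 1 places SPAQ at minus 3 months and about minus 1 week, and the Participants section makes eligibility depend on the SPAQ change over that period. Under Choice of outcome measure, direct measurement of activity and fitness is deliberately left until after randomisation.

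**The concern.** In a randomised trial, baseline differences between arms are chance. An observed imbalance is therefore a poor reason to choose covariates; the good reason is that a variable predicts the outcome. With an undefined trigger, someone must judge after seeing the data whether adjustment is needed, and the reader cannot tell in advance which number will be the main result.

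The list also passes over the covariate most likely to matter. With no baseline accelerometry, SPAQ is the closest available stand-in for a baseline value of the outcome. Every randomised participant should have it, because eligibility requires it. If it predicts 3-month counts, leaving it out widens the confidence interval for no saving. The same holds if it enters only when it happens to be imbalanced.

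**Working it through.** **Inputs from the Sample size section.** Difference 400,000 counts/week ("We assume a mean difference of 400,000 counts per week between the intervention and control groups"); SD 1.2 million ("assuming a standard deviation of 1.2 million counts/week"); 300 booster and 150 control evaluable; two-sided 5% t-test. Stated result: "the trial will have 90% power to detect this mean difference or greater".

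**Step 1: reproduce the plan's figure.** In millions of counts:

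- SE = 1.2 × √(1/300 + 1/150) = 1.2 × 0.1 = 0.12
- 0.4 / 0.12 = 3.333
- Power = Φ(3.333 − 1.96) = Φ(1.373) = 91.5% (91.4% with the noncentral t)

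The stated 90% holds for the unadjusted test and does not rely on adjustment.

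**Step 2: always adjust.** Let r be the correlation between the baseline covariate and 3-month counts. The article gives no r, so a range of 0.2 to 0.4 is assumed. Residual SD = 1.2√(1 − r²); power = Φ(3.333/√(1 − r²) − 1.96); 95% CI half-width = 1.96 × 0.12 × √(1 − r²); equivalent extra evaluable participants = 450 × (1/(1 − r²) − 1).

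| r (assumed) | Variance cut | Residual SD (million) | Power | CI half-width (counts/week) | Equivalent extra participants |
|---|---|---|---|---|---|
| 0 | 0% | 1.200 | 91.5% | 235,200 | 0 |
| 0.2 | 4% | 1.176 | 92.5% | 230,400 | 19 |
| 0.3 | 9% | 1.145 | 93.8% | 224,400 | 45 |
| 0.4 | 16% | 1.100 | 95.3% | 215,600 | 86 |

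**Step 3: adjust only on imbalance.** The article gives no threshold, so the simulation assumes adjustment when the covariate differs between arms at p < 0.05. It used 20,000 trials per setting at 300:150 with one baseline covariate. This is generous to the plan, because it lets SPAQ be the triggering variable. Monte Carlo standard errors are about √(0.915 × 0.085/20,000) = 0.2 percentage points for power and √(0.05 × 0.95/20,000) = 0.15 points for type I error.

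| r | Power: never adjust | Power: adjust on imbalance | Power: always adjust | Type I error: rule applied mechanically | Type I error: smaller p-value chosen |
|---|---|---|---|---|---|
| 0.2 | 91.62% | 91.75% | 92.61% | 4.98% | 6.02% |
| 0.3 | 91.15% | 91.51% | 93.61% | 5.00% | 6.68% |
| 0.4 | 91.47% | 91.89% | 95.07% | 4.66% | 6.98% |

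At r = 0.4 the rule gains 91.89 − 91.47 = 0.42 points, against 95.07 − 91.47 = 3.60 for always adjusting, or about 12% of the available gain. The reason is simple: with one covariate, a p < 0.05 trigger fires in about 1 trial in 20, and otherwise the unadjusted standard error is used.

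**The case against.** Much of the case for leaving the plan alone is sound.

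- **The t-test is always computed.** The Sample size section powers the trial on the same test ("as statistically significant at the 5% (two-sided) level using a two independent samples t-test"). A reader might infer that the primary estimate switches from t-test to regression. The text does not say that the regression replaces the t-test, only that the adjusted coefficient is then reported. What stands is the silence on which is primary.
- **Type I error.** A reader might infer that the conditional rule inflates it. Applied mechanically it does not: simulated error is 5.0% at r = 0.2 and 0.3 and 4.7% at r = 0.4. Inflation to about 6% to 7% needs someone to choose the more favourable result, and the article does not say that anyone may. Analysts are blind to allocation (Blinding section), which limits choice by direction. It does not prevent choice by p-value, and pooled groups in a 2:1 ratio can be recognised by size.
- **The precision loss is not a known quantity.** No correlation between SPAQ and accelerometry is given. Selecting participants on SPAQ level and change narrows its range and may weaken the correlation. At r = 0.2 the gain is one power point. The article also reports a suggested change of primary outcome to energy expenditure, for which r is equally unknown.
- **Missing data.** With 25-30% loss expected, a reader might object that an unadjusted test on observed data needs a stronger missingness assumption than a model conditioning on baseline predictors. That is so, but the plan already includes a sensitivity analysis that imputes missing accelerometry from baseline and follow-up data, which mitigates the point.
- **The list is illustrative.** The physical measurements are given as examples, so SPAQ is not expressly excluded. All the examples are body measurements, however, so it is fair to say that SPAQ is not named.

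Detail commonly left to an analysis plan would be no finding. Here the article itself states the rule, and the rule as stated is a poor one.

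**Conclusion.** The point holds as one of pre-specification and efficiency. Adjustment hangs on an undefined observation of imbalance, no single estimate is named as primary, and the most relevant baseline variable is not named for adjustment. The pre-specification defect holds whatever r is.

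The efficiency loss depends on the assumed r. For r of 0.2 to 0.4, prespecified adjustment would be worth 4% to 16% of variance, or about 1 to 4 power points on 91.5%, and the conditional rule recovers only a small part of it. The simulated figures also assume a p < 0.05 trigger on a single covariate.

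The documents do not support a conclusion that the trial is underpowered, that the t-test is invalid, or that the rule by itself inflates false positives. This should be changed, but nothing in the design fails without it.

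**What to change.** In Statistical methods, name one primary estimate in advance: the arm coefficient, with its 95% CI, from a linear regression of 3-month counts/week on arm (pooled booster against control). Always adjust it for a short fixed list that includes baseline SPAQ moderate or vigorous activity (about minus 1 week), age and sex. The minus-3-month SPAQ and BMI are optional additions. Report the unadjusted t-test difference and interval as a supporting analysis.

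Delete the imbalance condition here and where it recurs for the categorical and continuous secondary outcomes, and fix the adjustment in advance there and for full versus mini booster. Keep the planned imputation as a sensitivity analysis. If the primary outcome moves to energy expenditure, the same structure applies with that outcome.

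The cost is wording only. Table 1 already collects SPAQ before randomisation, the baseline summaries already include age, sex and BMI, and the sample size stays as it is.

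### Continuous secondary outcomes that have a baseline value should always be adjusted for that baseline, not compared by unadjusted t-test with adjustment only if imbalance is seen; for SF-12v2 plus 4 the main estimate is left open

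*Protocol article*

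**What the plan says.** All of this is in the protocol article.

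- **Statistical methods, list of secondary analyses at three and nine months.** Quality of life appears as "Change in health-related quality of life measured by changes in SF-12v2 plus 4 (converted to SF-6D" and the psychological outcomes as "Changes in psychological measures of motivation, intention and stages of change, and self-efficacy". Self-reported activity is also described there as a change.
- **Statistical methods, paragraph on continuous secondary outcomes.** It gives two examples, the SF-12v2 plus 4 dimension scores and the distance in the 12 minute walk test, both at three months. The method is: "A two independent samples t-test will be used to compare mean outcomes between the booster and control groups in this parameter". Nine-month outcomes, and the comparison of the two boosters, are handled in the same way.
- **Adjustment.** Multiple regression or ANCOVA is used only if the groups are found to differ at baseline on demographic, physical or quality of life measurements. The article does not say what counts as a difference.
- **Outcomes, Table 1.** SPAQ, BREQ-2, EXERT, SF-12v2 plus 4, and height and weight are all recorded at or before randomisation. The 12 minute walk test and accelerometry are recorded only at three and nine months.

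The article does not say which of the change, the follow-up mean or the adjusted difference is the main result for any of these outcomes.

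**The concern.** Three points come together.

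1. For SF-12v2 plus 4, one paragraph points to change and the next to the follow-up value. Two analysts following the text could report different main estimates.
2. Adjustment depends on what the baseline table shows, with no threshold. The listed triggers do not include SPAQ, BREQ-2 or EXERT, and adjustment is for the trigger variables. Even a triggered ANCOVA therefore need not contain those outcomes' own baselines.
3. The most useful covariate for each outcome has already been collected, but by default it is not used.

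At stake are the precision of the secondary results and the clarity of which number is the headline.

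**Working it through.** **Inputs from Sample size.** "With 450 subjects (300 intervention: 150 control), the trial will have 90% power to detect this mean difference or greater"; "We assume a mean difference of 400,000 counts per week between the intervention and control groups"; "assuming a standard deviation of 1.2 million counts/week"; "statistically significant at the 5% (two-sided) level using a two independent samples t-test". Also "Assuming an approximate 25-30% loss to follow-up by six-months", so 600 × 0.75 = 450 analysed.

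**Input not in the documents.** The baseline to follow-up correlation r. I take 0.3 to 0.8.

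**Step 1: the plan's own figure.** Standardised difference = 400,000 / 1,200,000 = 0.333. SE in SD units = √(1/300 + 1/150) = 0.10. Power = Φ(0.333/0.10 − 1.96) = Φ(1.37) = 0.915 (0.914 by noncentral t), against the stated 90%. It reproduces. It concerns accelerometry, which has no baseline, so nothing below alters it.

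**Step 2: precision.** With equal SDs at both times, the variance of the treatment difference relative to the follow-up t-test is:

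- follow-up mean: 1
- change: 2(1 − r)
- ANCOVA: 1 − r²

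The ANCOVA SE is thus √(1 − r²) times that of the follow-up t-test and √((1 + r)/2) times that of the change t-test. The matching N is 450(1 − r²).

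| r | Variance, change | Variance, ANCOVA | SE cut vs follow-up | SE cut vs change | ANCOVA N matching t-test on 450 |
|---|---|---|---|---|---|
| 0.3 | 1.40 | 0.91 | 5% | 19% | 410 |
| 0.5 | 1.00 | 0.75 | 13% | 13% | 338 |
| 0.7 | 0.60 | 0.51 | 29% | 8% | 230 |
| 0.8 | 0.40 | 0.36 | 40% | 5% | 162 |

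Below r = 0.5 the change score is less precise than the follow-up mean.

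**Step 3: power for an assumed effect of 0.2 SD, 300:150.** Follow-up t-test: Φ(0.2/0.10 − 1.96) = 0.52 at every r. Multiplying the SE by the square root of the relative variance gives, at r = 0.3, 0.5, 0.7 and 0.8:

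- change: 0.39, 0.52, 0.73, 0.89
- ANCOVA: 0.55, 0.64, 0.80, 0.92

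**Step 4: how far the two estimates can part.** They differ by exactly the baseline mean difference d, whose SE is 0.10 SD. Given d, the follow-up estimate is off by r·d, the change estimate by (r − 1)·d, and ANCOVA by nothing. For example, with d = 0.15 SD and r = 0.6 the errors are +0.09 and −0.06 SD. That imbalance is 0.15/0.10 = 1.5 SE (p about 0.13), so a 5% significance trigger would not fire.

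**Step 5: simulation.** 4,000 trials per setting, 300:150. The adjust-if-imbalanced rule is given an assumed trigger of p < 0.05 on the outcome's own baseline.

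| | r = 0.5 | r = 0.7 |
|---|---|---|
| Type I error, triggered rule | 0.046 | 0.033 |
| Power at 0.2 SD, triggered rule | 0.53 | 0.52 |
| Power at 0.2 SD, ANCOVA always | 0.64 | 0.80 |
| Follow-up and change tests disagree on significance, no effect | 8.6% | 9.0% |
| Same, 0.2 SD effect | 33% | 39% |
| At least one of the two significant, no effect | 9.7% | 9.6% |

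The triggered rule is conservative and gives up nearly all the gain that ANCOVA offers.

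**The case against.** Several objections have force.

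- **The double specification is narrow.** A reader might infer that every secondary outcome with a baseline is declared twice, once as change and once as a follow-up mean. The text does not support that. Only SF-12v2 plus 4 appears in both places, and even there the change item refers to SF-6D and the t-test paragraph to dimension scores. Self-reported activity and the psychological measures are stated only as change; they reach the follow-up t-test because that paragraph's outcomes are given as examples. EXERT and BMI are named in neither. This objection stands and limits the point.
- **A compatible reading exists.** The list may say what is compared and the later paragraph how, so that the t-test is on mean change. This is possible, but the paragraph speaks of outcomes at three months. On this reading ANCOVA still cuts the SE by 5% to 19% over the assumed range.
- **Nothing is biased or invalid.** This is correct. Both estimators are unbiased over randomisation, and the triggered rule did not inflate type I error in the simulation. The roughly 9.6% is the chance that one or other of two tests is significant, not the error rate of the plan.
- **The trigger may catch an imbalance.** It may, for quality of life. With no threshold stated, nobody can say when.
- **Analysts are blind to allocation (Blinding).** This lowers the risk of a selective choice, but does not say which estimate is the main one.
- **The correlation is unknown.** This is true. It may be lowest for SPAQ, because entry required a SPAQ increase measured about a week before randomisation. At r = 0.3 the gain over the follow-up t-test is only about 5%.
- **The economic analysis might seem to be affected.** It is not: Statistical methods gives the QALY comparison its own area-under-the-curve method with its own baseline adjustment.

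**Conclusion.** The point holds as an improvement that costs nothing, confined to continuous secondary outcomes with a baseline value. The article fixes an unadjusted t-test as the default and a data-driven trigger without a criterion, and for SF-12v2 plus 4 it leaves the main estimate open. Because it states these methods outright, this is not detail left to an analysis plan.

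The loss is in precision and clarity, not validity. Its size depends on r, from slight at 0.3 to large at 0.8. The figures further assume equal SDs at both times, a linear relation, and the 300:150 analysed numbers that the article uses for the primary outcome; the 0.2 SD effect and the p < 0.05 trigger are also assumptions.

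A reader might go further and conclude that the plan produces conflicting results or undermines the trial's power. The documents do not support that: the two estimates can differ only by the chance baseline difference, and the primary outcome has no baseline.

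**What to change.** In Statistical methods, state one main estimate per outcome and time point. For SPAQ, SF-12v2 plus 4 scores, BREQ-2, EXERT and BMI, at three and at nine months, this is the difference between groups in the follow-up value from ANCOVA, always adjusted for that outcome's own baseline, with its 95% confidence interval. Then:

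- remove the imbalance trigger for these outcomes;
- present change from baseline descriptively only;
- for SPAQ, say which of the two pre-randomisation values in Table 1 is the baseline;
- use the same model for the comparison of the two boosters.

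The 12 minute walk test is outside this change. The primary model cannot supply a fixed covariate list, since its own adjustment is also conditional, so the rule should rest on the outcome's own baseline alone.

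The cost is analysis wording. No extra data or participants are needed, because Table 1 already schedules every baseline required.
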